### Secondary Objective

In accordance with the Fifth National Mental Health and Suicide Prevention Plan [9], the secondary objective of this clinical trial is to reduce the rate of suicidal thoughts and/or behaviors by promoting access to comprehensive services and reducing barriers to care, as well as improving service quality and evidence-based clinical interventions. It is hypothesized that use of the platform within traditional mental health services will facilitate earlier identification and rapid service response (eg, earlier appointment with a health professional) to high levels of suicidal thoughts and/or behaviors.

InnoWell Platform functionality.Multidimensional assessment across a range of domains (eg, sleep, anxiety, mood, physical health)Suicidal thoughts and/or behaviors and at-risk mental state identification and subsequent escalation to required interventionDashboard of results across the range of biopsychosocial domainsAlgorithms to determine severity of needs across these biopsychosocial domainsAlgorithms to allocate clinical stage and suggested levels of careReal-time data tracking and interactive progress reportShared care planning between treating health professional and consumerVideo-visit with a health professionalSupport person input and health information sharingCoordination of care across multi-disciplinary servicesAggregate service performance indicator dashboard

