### Participant Procedures

Participants will use the platform of their own accord as part of their standard clinical care with the mental health service. No other participation is required. All survey data are part of the functionality of the platform, which participants complete as part of standard clinical care through their service. The surveys provide assessment across a range of biopsychosocial domains, including psychological distress, suicidal thoughts and/or behaviors, social and occupational functioning, depressed mood, anxiety, sleep-wake cycle, social connectedness, psychosis-like experiences, mania-like experiences, alcohol use, tobacco use, self-harm, physical health, posttraumatic stress, eating behaviors, and body image. These domains, along with the associated surveys configured in the platform, are determined by services, in conjunction with the researchers to meet the needs of their consumers. Table 1 provides an example of the surveys that may be included across a sampling of biopsychosocial domains.

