Given the emphasis on suicide prevention, the InnoWell Platform has been built to include immediate access to crisis support options. At any time when engaging with the platform, a participant has access to the “I need help now” button (see Figure 3), which provides contact details for crisis services (eg, Lifeline, Beyond Blue, and Kids Helpline). As described previously, these support options also appear as a pop-up directly after the participant scores low, moderate, or high on the suicidal thoughts and/or behaviors health card. When a participant scores high on this health card, a notification of suicide risk is also triggered for the treating health professional requiring clinical action.

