### Configuration

The InnoWell Platform is highly configurable, allowing each service to adapt the technology to the needs of its consumer base. Although there is a set of core biopsychosocial domains that all services will be encouraged to assess (ie, psychological distress, suicidal thoughts and/or behaviors, psychosis-like experiences, mania-like experiences, social and occupational functioning, self-harm, tobacco use, alcohol use, social connectedness, depression, anxiety, and posttraumatic stress), the measures used to evaluate these areas can be tailored to the service. Similarly, the algorithms used to derive the thresholds for each domain will be based on the most appropriate psychometrics for that population (eg, young people, veterans, and older adults). As the platform is implemented across multiple health services and accumulates more data, these algorithms will become digitally smart.

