#### Secondary Outcome

Service-level performance data regarding improvements in safety and clinical quality will be derived from the platform, with an emphasis on identification and rapid response to consumers endorsing suicidal thoughts and/or behaviors (see Figure 4). Outcomes will include the percentage of consumers endorsing suicidal thoughts and/or behaviors across 4 severity levels (ie, none, low, medium, and high) at service entry, the number of suicide escalations (ie, notifications to health professionals) for a specific period and during an entire episode of care, and time between suicide escalation and an action by a health professional (eg, call to consumer, schedule follow-up appointment, and contact emergency services).

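### Two of the three listed secondary safety outcomes are hard to interpret as defined: escalations are a raw count with no divisor, and time to action has no companion measure of alerts that receive none

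*Protocol article*

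**What the plan says.** The protocol article, under Secondary Outcome, names three service-level safety measures:

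- The first is the share of consumers in each of four suicidality levels when they enter the service.
- The second is a count, worded as "the number of suicide escalations (ie, notifications to health professionals) for a specific period and during an entire episode of care", with nothing said about a divisor.
- The third is an interval, worded as "time between suicide escalation and an action by a health professional", with a few examples of what counts as an action.

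Other sections say how an escalation comes about. In The InnoWell Platform and in Participant Procedures, alerts come from self-report surveys. When a participant scores high on the suicidality card, "a notification of suicide risk is also triggered for the treating health professional requiring clinical action". Survey completion is voluntary: "Participants will use the platform of their own accord as part of their standard clinical care with the mental health service". No survey schedule is given. Under Configuration, services are encouraged, not obliged, to assess the core domains, and "the measures used to evaluate these areas can be tailored to the service". Under Sample Size, enrolment has no limit in either direction.

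The Secondary Objective section gives two aims. One is that "the secondary objective of this clinical trial is to reduce the rate of suicidal thoughts and/or behaviors". The other is a hypothesis that the platform will lead to earlier detection of high suicidality and a faster response to it.

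**The concern.** The first measure has a denominator. The second has a time window but is not divided by anything. No alert can occur without a completed survey, so the number of alerts depends on how many consumers a service has, how often they complete the survey and how long they stay in care, as well as on their risk. A change over time, or a difference between services, could come from any of these.

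One consumer can also contribute several alerts. The platform description makes a suicide attempt in the preceding three months a trigger. Nothing in the article says that a second survey completed within that window would not raise a second alert for the same attempt.

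The third measure is an interval that ends at an action. An alert that is never acted on has no such interval, and no listed outcome reports the share of alerts acted on. Yet the article describes the notification as one that requires action, and rapid response is part of the hypothesis. The event that matters most for safety, an alert with no response, therefore has no explicit place among the listed outcomes.

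**Working it through.** The article states no event rate, survey frequency, response time or share of unanswered alerts, so there is no figure of its own to reproduce. All inputs below are assumptions, chosen only to show how each measure behaves.

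**Escalation count.** Expected alerts = N × s × p, where N is consumers, s is completed suicidality surveys per consumer and p is the chance of an alert per completed survey. Assume N = 200 and p = 0.10.

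| s | Expected alerts | Alerts per 100 surveys |
|---|---|---|
| 0.5 | 200 × 0.5 × 0.10 = 10 | 10 |
| 1 | 200 × 1 × 0.10 = 20 | 10 |
| 2 | 200 × 2 × 0.10 = 40 | 10 |
| 4 | 200 × 4 × 0.10 = 80 | 10 |

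The risk per survey is the same in every row. The count rises eightfold because survey use does.

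Episode length works the same way. At one survey a month and p = 0.10, alerts per consumer are 0.2, 0.3, 0.6 and 1.2 for episodes of 2, 3, 6 and 12 months. The rate is 0.10 per consumer-month throughout.

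The two divisors do different work. Consumer-time removes service size and episode length. Completed surveys also remove survey frequency: if the four rows of the table covered equal follow-up, their rates per consumer-month would still differ eightfold.

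**Time to action.** Suppose a share u of alerts is never acted on, and times among the rest are exponential with a median of 1 day, so λ = ln 2 per day. The proportion of all alerts acted on by time t is (1 − u)(1 − e^(−λt)). Setting this to 0.5 gives the all-alert median, t = −ln(1 − 0.5/(1 − u))/λ. For u = 0.4: 0.5/0.6 = 0.833, and −ln(0.167)/0.693 = 2.58 days. By 2 days, 1 − e^(−2λ) = 0.75 of the actioned alerts have been acted on, so the share over all alerts is 0.75(1 − u).

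| u | Median, actioned only (days) | Median, all alerts (days) | Acted on within 2 days, actioned only | Acted on within 2 days, all alerts |
|---|---|---|---|---|
| 0% | 1.00 | 1.00 | 75% | 75% |
| 10% | 1.00 | 1.17 | 75% | 67.5% |
| 20% | 1.00 | 1.42 | 75% | 60% |
| 30% | 1.00 | 1.81 | 75% | 52.5% |
| 40% | 1.00 | 2.58 | 75% | 45% |
| 50% | 1.00 | not reached | 75% | 37.5% |

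The medians scale with whatever actioned-only median is assumed. A summary over observed intervals stays the same however many alerts go unanswered.

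**The case against.** Much can be said for the article as it stands.

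- **Unanswered alerts.** A reader might infer that they are dropped, so that the outcome hides them. The text does not say so. It names a start and an end event, as any time-to-event outcome does, and gives no summary statistic or exclusion. Censoring rules and the handling of repeat alerts commonly sit in the full protocol or analysis plan, which are not shown. This stands: the understatement is conditional on how the interval is summarised.
- **Direction of benefit.** A reader might also infer that a service gains by surveying little. That needs fewer alerts to count as better. The rate-reduction objective points that way and the earlier-detection hypothesis points the other way. Secondary Outcome fixes no direction. This stands too; the supportable claim is that the count cannot be interpreted either way without exposure.
- **Use of the count.** A raw number is a legitimate measure of workload. The between-group tests in Data Analysis are described for clinical outcomes, and nothing states that escalation counts will be ranked across services. This is fair, but the count is presented under improvements in safety and clinical quality, a use that needs a divisor.
- **Open list.** The outcomes are introduced as an inclusive list, and user engagement is to be described elsewhere. A share acted on is therefore not ruled out, but it is not listed either.
- **Size.** Every magnitude is assumed. Because alerts are described as requiring action, a large unanswered share would be a marked departure from the described process, and the article gives no evidence of one.

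What survives concerns the outcome definitions themselves, not detail deferred to an analysis plan: one outcome is fixed as a bare number, and the only response measure is an interval with no accompanying proportion.

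**Conclusion.** The point holds for two of the three listed safety outcomes. With voluntary surveys and open enrolment, an undivided escalation count cannot separate risk from survey use, service size and episode length, so it cannot support a statement about risk or a fair comparison across services. Time to action, reported alone, says nothing about alerts that receive no action, and it would understate response time if only observed intervals were summarised.

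The size of either effect in this trial is unknown. The figures worked above rest on assumed survey use, alert probability, exponential response times and unanswered shares; they show the mechanism and do not estimate the bias. The primary outcome, agreement on clinical stage, is not affected. This is a cheap improvement.

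**What to change.** In Secondary Outcome:

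1. Keep the number of escalations, labelled as a workload measure. Add escalations per completed suicidality survey and per consumer-month.
2. Define the response outcome as time to first recorded action over all escalations, by Kaplan-Meier or cumulative incidence. Retain un-actioned alerts to episode end or data cut, and report the proportion acted on by stated times.
3. State that the analysis allows for repeated alerts from one consumer. The choice of model can be left to the analysis plan.

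This changes the wording of the outcomes and adds a little analysis work; it alters no clinical procedure. Response times may look slower. The rate per survey can itself be distorted if higher-risk consumers are surveyed more often, which is why both divisors are needed. Censoring at episode end may be informative, so the proportion acted on should be read alongside the curve. The article shows that the platform displays time since each survey, but it does not say that calls, appointments and emergency contacts are time-stamped. That should be confirmed before the definition is fixed.

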### Data Collection, Management, and Security

All collected data are stored in the platform database that resides in the Google Cloud Platform (in Sydney, New South Wales) and the encrypted backup database that resides in the Amazon Web Services platform (in Sydney, New South Wales). The researchers’ access deidentified clinical trial data using straight-through digital processing methods such that a copy of clinical trial data (at any point in time) can be automatically moved from the platform database to a specified secure University of Sydney network server in one go.

This trial will be conducted in accordance with the Privacy Act of 1988 [31]. Upon consenting to participate in the clinical trial, participants will be assigned a unique identifier (Version 4 UUID), which is automatically generated by the platform and stored within its database. A Version 4 UUID is a universally unique identifier that is generated using random numbers. Importantly, the unique identifier will be used to identify a participant in all research studies of the InnoWell Platform should they be a consumer at more than 1 participating center. In addition, researchers will assign all participants with a Study ID number within deidentified clinical trial datasets. These Study ID numbers will be maintained separately from the data collection process and used for statistical analysis purposes only. All data are backed up hourly in a secure, long-term storage on Google’s Infrastructure.

### Data Analysis

Scientific validity will be evaluated using interrater reliability statistical methods, such as Cohen kappa coefficient, to quantify the degree of agreement within and among the 4 ratings of stage-based stepped care (ie, platform-generated, health professional allocated, in-service multidisciplinary consensus, and independent expert-clinician reference group). The clinical performance, including aspects of safety, of the platform will be evaluated using aggregate data derived from clinical rating scales completed by the consumer and health professional to measure and track health domain intensity, frequency, quality, and change over time, and aggregate service-level performance data, including safety and clinical quality (eg, time to first assessment, service accessibility, wait time for clinical intervention, service efficiency, and user satisfaction). Within- and between-group analyses using multivariate statistics (eg, multivariate analyses of variance, Kruskal-Wallis test) will be computed to evaluate differences in clinical outcomes among services and among population groups. In addition, reliable change and effect-size scores will be calculated to determine clinical improvement over time for consumer data and then aggregated for service-level outcome data. Analytical validity will be assessed using trends only (ie, descriptive statistics) as a means to determine user engagement and overall effectiveness of the technical performance of the platform.

### Ethics Approval

This trial has been approved by the Northern Sydney Local Health District Human Research Ethics Committee (NSLHD HREC), reference number HREC/17/HAWKE/480.

**Figure 4 figure4:**
[figure not shown]
Hypothetical service-level performance data related to safety.

## Discussion

### Person-Centered Care

At its core, the InnoWell Platform is designed to promote person-centered health care and assist clinical practices that place consumers as equal partners in health care decision making. The platform is also intended to help minimize the variability in care provision between health professionals and services by supporting clinical judgement with data. In addition, the platform aims to maximize the use of available resources and minimize duplication of services and wastage of time for all users, including consumers, health professionals, and service staff.

### Feasibility of Implementation With Service

Before implementing this clinical trial, a thorough assessment of the feasibility of deploying the platform within each service (or participating center) is required [32,33]. This includes an understanding of the basic service attributes (eg, type of service, qualifications of health professionals, service location(s), and information and communication technology systems), as well as the identified needs of the organization that will be met by the platform. In other words, what problem(s) will the technology address? The fit of the InnoWell Platform to the values, priorities, and strategic plan for the service and the readiness of the service to adopt the technology also need to be examined. As the platform is customizable, it is necessary to identify in what way the technology needs to be modified or adapted to fit the service and its consumers. Finally, key to this process is the engagement of critical stakeholders who can drive the adoption of the platform, identify facilitators, mitigate barriers to implementation, and champion the technology among frontline staff whose practice will be most affected. The effective deployment of the platform will be supported by implementation officers embedded within the services. These people will ensure that research protocols are adhered to and report any adjustments that might be necessary; they will monitor, catalogue, and report on the progress of the implementation to key trial leads; they will collect data at the participating center, relating to facilitators or barriers of implementation from clinical and administrative staff; they will assist with preparation of and delivery of training to relevant personnel regarding information essential to site-specific implementation; they will ensure that the platform accurately and consistently reflects the research data; they will ensure that all participants’ safety and well-being are first priority, by liaising with technology specialists, the researchers, and the relevant participating center, and by following established ethical protocols.

### Ongoing Development of Functionality

Qualitative and quantitative data will be gathered from all users of the platform, including consumers, as well as health professionals and service staff, to inform the iterative redevelopment of the platform, including site-specific customization of any new required functionality, as well as (re)configuration of content, questionnaires, and algorithms. Furthermore, the data collected during iterative user-testing sessions (covered under site-specific ethics approvals from relevant Human Research Ethics Committees) will help to monitor, evaluate, and provide ongoing feedback about the quality, acceptability, and usability of the platform for continuous improvement of the platform.

### Future Research

This clinical trial will be run in parallel with a series of participating center-specific impact evaluation studies. These adjunctive studies will focus on gathering data through Web-based questionnaires, as well as workshops and semistructured interviews with service staff (ie, health professionals, managers, and administrators) relating to the impact of embedding the InnoWell Platform in their service. Topics to be covered will include digital readiness and competence, the impact of the platform on the service, the social return on investment, and the quality, usability, and acceptability of the platform. In addition, workshops will also offer the opportunity for researchers to introduce and provide brief training to service staff relating to new functionality that will be incorporated into the platform at quarterly intervals. Separate ethics approvals will be sought for these studies.

## Abbreviations

BMC: Brain and Mind Centre
eHealth: electronic health
NMHC: National Mental Health Commission
PwC: PricewaterhouseCoopers
